##### Social beacon network

Social networks are also assessed with Bluetooth technology to detect proximal peers via smartphones. The *Social Beacon Network* is an innovative unobtrusive way to measure physical distances between all participants. The research smartphones scan and detect other participants’ phones that are within Bluetooth range (approximately 10 m). When participants are within close proximity for more than half an hour, two questions are triggered to check whether participants are actually spending time together and to avoid measurement error caused by participants passing by accidentally while the phone was scanning the proximity (‘*Are you spending time with someone?*’ If so, ‘*With whom are you spending time?’*). In addition, they are asked to indicate what they are doing in an open-ended format. The Social Beacon Network provides one way of validating the sociometric questions and the social networks created from these items.

In conclusion, the *Social Beacon Network* can provide insights into the relative frequency of interactions between individuals (with multiple measurement points) during the day, which complement the sociometric items, which are only assessed once per data collection wave. This unobtrusive research method requires new data management strategies that are being developed during this project.

#### III. Activity tracking bracelet

Participant’s activity tracking bracelet *Fitbit Flex* (i.e., accelerometer) measures physical activity as the number of steps in continuous time (i.e., minute to minute). The bracelet calculates active minutes using metabolic equivalents (METs). METs are widely used as indicators for exercise intensity measuring in a comparable way among persons of different weights. The intensity of the activity is categorized in sedentary activity, light intensity activity, moderate intensity activity, and vigorous intensity activity, in line with the Center for Disease Control’s (CDC) recommendations [41]. The number of steps each day, as well as the number of minutes in each of the PA categories recorded on each Fitbit is automatically transferred to the *MyMovez* app. The first and the last day of the measurement period are excluded because the participants do not wear the bracelet the entire day (i.e., the research materials were given to and received from participants during school hours).

#### IV. Real-time data

The Netherlands is famous for its cycling culture and almost every household owns at least one bicycle [42]. Because the wearable accelerometer is worn at the wrist, the device does not detect physical activity while riding a bicycle. Therefore, to have a complete assessment of PA for Dutch youth, cycling data is obtained to complement the activity detected by the accelerometer. On the basis of the velocity patterns measured by the accelerometer in the smartphone, the software estimates the location of smartphone. Based on the GPS locations of the beginning and the end of the cycling trip, the average speed and distance is calculated.

The GPS data also provide information about the physical environment of the participants to investigate the proximity of facilities conducive to snack consumption and physical activity (e.g., snack bars, swimming pools, parks, etc.).

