### Design

The *MyMovez* project consists of a cross-sequential design, following two cohorts (8-12 and 12-15 y/o) over 3 years. Five waves of data are collected during the months February/March 2016 (w1), April/May 2016 (w2), June/July 2016 (w3), February/March 2017 (w4) and February/March 2018 (w5). Outcome measures involve social network characteristics, social media use, physical activity, beverage and snack consumption.

A power analysis was performed based on results from a previous cross-sectional longitudinal study that investigated energy balance behaviors among Dutch youth [35]. It was assumed that obesity inducing risk behaviors are present among approximately 40% of adolescents, and with a statistical significance level of .05 and 80% power, a sample size of 600 participants would be sufficient for the cross-sectional and longitudinal study. This sample size was also deemed appropriate for social network analyses, which require approximately 20-25 complete classroom networks. Assuming that Dutch school classes exist of an average of 25 kids, this would produce a sample between 500 and 625 students. Taking into account a conservative 40% attrition rate [36] we aimed to include 850 participants and oversampled the high school population because this age group is more likely to change schools or classes or drop out while followed during a period of three years. In the end, this led to recruitment of a sample of 953 participants.

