Furthermore, the *Wearable Lab* allows for the collection of other novel types of data such as photo queries and global positioning system (GPS) data. For example, photo data are coded and used for machine learning purposes (e.g., coding of food or media use pictures) contributing to the examination of youth’s diets, social media behavior and other daily activities [37]. The GPS data provides information about cycling^1^ (the activity tracker only counts the amount of steps and the intensity) and the physical environment, by linking these to Geographic Information System (GIS) data in which youth are exposed to food and PA related facilities [38]. All together, the *Wearable Lab* allows for the collection of a comprehensive set of data that provides the opportunity to address all of the project’s research goals.

Participants receive surveys, photo questions or notifications on daily randomized or fixed time points. In addition, the researchers can personalize for each school class the time schedule in which participants are allowed to receive questions and notifications (i.e., before and after school and during school breaks only). Regularly used answering categories are already available in the backend of the app which saves researchers time in programming the surveys. In addition, it is possible to include follow-up or feedback loops based on answers to closed questions or PA measured by the activity tracker, send jokes/memes, riddles, and *MyMovez* news flashes. To keep the participants engaged, the app also includes two games (Zoko and Snake; which are allowed to play 5 min./hour) and participants can create and adjust their own avatar (e.g., face characteristics, hairstyle and -color, and additional attributes such as animals, music instruments, fruits, or sport gear). Participants also have the opportunity to chat with their classmates or with a researcher to ask research related questions, report misconduct, or ask for help.

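### Cycling distance and speed are derived from trip end points, which understates indirect rides and gives zero for a loop logged as one trip

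*Protocol article*

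**What the plan says.** All of this is in the protocol article.

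- IV. Real-time data explains why cycling needs its own measure: with the bracelet on the wrist, "the device does not detect physical activity while riding a bicycle". The purpose is broad: "to have a complete assessment of PA for Dutch youth, cycling data is obtained to complement the activity detected by the accelerometer".
- The same section gives the method in two sentences. The first is a location step: "On the basis of the velocity patterns measured by the accelerometer in the smartphone, the software estimates the location of smartphone". The second is the calculation: "Based on the GPS locations of the beginning and the end of the cycling trip, the average speed and distance is calculated". It names no waypoints, track, route matching or odometer value, and neither does any other section. It does not define when a trip begins or ends.
- Physical activity is an outcome. Under Design: "Outcome measures involve social network characteristics, social media use, physical activity, beverage and snack consumption".
- III. Activity tracking bracelet says that the bracelet yields daily steps and minutes in each intensity category.
- GPS also has a second use: "The GPS data also provide information about the physical environment of the participants".

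**The concern.** The path ridden is never shorter than the straight line between its ends, so a distance built from end points can err in one direction only. Average speed inherits the error, because the elapsed time is real while the distance is too short.

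The bracelet cannot correct this, since by the article's own account it does not register cycling. What is at stake is a component of the physical activity outcome that was added to make that outcome complete.

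The size of the error depends on how direct the route is. Directness plausibly differs between street layouts, and between a school commute and a recreational ride. The project relates activity to the physical environment and, under Strategy of analysis, examines similarity of behaviour among peers. An error that follows the environment, or that classmates on the same roads share, could shift those associations and not merely add noise.

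**Working it through.** The article gives no figure for this measure, so there is none to reproduce. The check is geometric.

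**Inputs**

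- Method: end points of each trip (IV. Real-time data).
- c, the ratio of ridden to straight-line distance: not given. Assumed 1.2 to 1.4, with 1.0 to 2.0 as the wider range.
- True speed of 15 km/h and a destination 3 km away in a straight line: illustrations only.
- Distance between end points taken as a straight line, and trip duration taken as correct: both assumptions.

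**Indirect routes**

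Recorded distance / true distance = 1/c, so the understatement is 1 − 1/c. Recorded speed = true speed / c.

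| c | Understatement | 15 km/h is recorded as |
|---|---|---|
| 1.0 | 0% | 15.0 km/h |
| 1.1 | 9.1% | 13.6 km/h |
| 1.2 | 16.7% | 12.5 km/h |
| 1.3 | 23.1% | 11.5 km/h |
| 1.4 | 28.6% | 10.7 km/h |
| 1.5 | 33.3% | 10.0 km/h |
| 2.0 | 50.0% | 7.5 km/h |

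**Rides that return to their start**

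Take 3 km straight-line each way with c = 1.3. The true length is 2 × 3 × 1.3 = 7.8 km.

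- Logged as one trip: start and end coincide, so distance is 0 km and speed is 0. Understatement 100%.
- Split at the stop into two trips: 2 × 3 = 6.0 km. Understatement 1 − 6.0/7.8 = 23.1%.

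The result therefore turns on how a trip is defined, which the article does not say.

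**Does the error cancel in comparisons?**

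If c were the same for everyone, all distances would be scaled by 1/c, and correlations and ranks would not change. If c differs between groups, it does not cancel. With 7.8 km of one-way riding in each of two neighbourhoods, one at c = 1.2 and one at c = 1.4, the records are 7.8/1.2 = 6.5 km and 7.8/1.4 = 5.6 km. That is an apparent difference of 1 − 1.2/1.4 = 14.3% where none exists. This shows the mechanism only; the article has no data on how c varies.

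**Duration**

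An average speed cannot be formed from two locations without the time between them. A trip duration must therefore already be available, and it does not depend on the shape of the route.

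**The case against.** The strongest reply is that the text names the end points but does not say that they are the sole input or that the distance is a straight line. The preceding sentence describes a software step using the phone's accelerometer, which might feed the calculation. A footnote is attached to cycling under Wearable lab, and its text was not available for this check. A condensed article may also leave the algorithm to fuller documentation. This stands as a limit on certainty, and the point is therefore made on the plain reading. It does not remove the point: the article states a basis for the calculation, and that basis cannot recover the path ridden.

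A reader might infer several stronger things that the document does not support:

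- That round trips always count as zero. This holds only for a ride logged as one trip; a ride to school and a ride home logged separately do not give zero.
- That every indirect route is understated. This needs straight-line distance. A route lookup between the end points would miss only riding beyond the looked-up route.
- That this is the only source on cycling. Table 1 lists self-report instruments for habitual activity and items on daily activities and sports, and the article does not say whether they cover cycling. It is the only device-based source described.
- That the associations are biased. No section says that cycling distance or speed, as opposed to duration or presence of cycling, enters the physical activity outcome, and a detour ratio common to all would leave correlations intact. Bias is possible, not demonstrated.

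It is also fair that 1.2 to 1.4 has no source in the document, and that the planned GIS linkage is described for facilities and environment, not for cycle routing.

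**Conclusion.** The point holds in conditional form. Followed as written, the stated method understates cycling distance and average speed on indirect routes: by 17% to 29% if straight-line distance is used, c lies between 1.2 and 1.4 and duration is correct, and by 0% to 50% over c from 1.0 to 2.0. A loop or out-and-back ride logged as a single trip gets zero for both; how often this occurs cannot be judged from the article. The direction of the error follows from geometry; its size rests on the assumed ratio. An effect on the environmental and peer-similarity analyses is plausible but not shown. The point is worth acting on because the measure exists to complete an outcome, the bracelet cannot compensate, and a quantity free of the route error is already implied by the calculation of speed.

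**What to change.** - Use the duration of the detected cycling trip as the primary cycling quantity, alongside the bracelet's active minutes, which are in the same unit.
- Report distance and speed from the summed GPS track if intermediate fixes are stored. The environmental use of GPS suggests that they may be, but the article does not confirm it.
- Where only end points exist, use a shortest-route distance between them and label it, and the speed derived from it, as a lower bound.
- Set distance and speed to missing, not zero, when start and end coincide. The ride still counts through its duration.
- State when a trip starts and ends, including whether a stop splits it, and which distance is used.

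The cost is extra processing of data already collected and, where no track exists, missing distance and speed for loop rides. Route lookup would be an addition to the GIS linkage as described. No new measurement is needed.

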#### V. Photos

Participants receive two photo questions at random time points during the day in each data wave from day 2 to 5. They are asked to make a picture of what they are doing at that moment [43]. When the photo is taken, a question is triggered so that the participants can categorize the photo into ‘reading or doing homework’, ‘watching TV/tablet/computer’, ‘gaming’, ‘having a snack, drink or meal’ or ‘other.’ Depending on their answer, they are directed to follow-up questions to explain their activity in further detail (e.g., which game they are playing) and describe what is in the picture they photographed. In addition, the photos are coded for detailed content. Before the coding of the photo data by independent coders, a trained researcher of the *MyMovez* team inspected all the photos to ensure that no identifiable or sensitive information is being shared. A codebook is available on request.

#### VI. Social buzz chats

Starting in January 2017 (Wave 4), participants are able to chat with each other in the social media platform *Social Buz*z, which is a safe chat environment within the *MyMovez* app. *Social Buzz* involves three chat levels, with separate time lines. Participants are able to talk with their classmates 1-on-1 (individual time line in the *MyBuzz*), with their classmates in a group chat (class-level time line in the *ClassBuzz*), and with the *MyMovez* research team (the *MyMovez* time line). Besides chat conversations, participants have the opportunity to like, share and respond to messages or images sent by their peers or by the *MyMovez* team. Images can be sent from picture folders that are composed by the *MyMovez* team. By January 2018, participants will also be able to like, share and comment on short video clips. For privacy reasons, it is not possible for participants to send pictures, images, or videos they make or create themselves. The *MyMovez* research team has the opportunity to send messages to the participants as well (individual level or class level).

Within the *Social Buzz* environment, we integrated the option for participants to flag inappropriate behavior. When participants use the flag button, for example, when they see a message that they do not think is appropriate, researchers from the *MyMovez* team receive a notification so that they can solve the situation immediately. *MyMovez* team members have the possibility to remove specific messages that are flagged, block specific users, or shut down the entire *Social Buzz* option for a class. The *Social Buzz* is also very useful for *MyMovez* researchers when they want to communicate with the participants, for example to remind them to hand in their *Wearable Lab*.

The purpose of the *Social Buzz* is two-fold: On the one hand, it reinforces participant’s engagement in the project, on the other hand it provides the opportunity to investigate social media use and social network relations (i.e., who are connected to each other). In Phase II, the *Social Buzz* will be used to implement and test intervention messages which will provide interesting insights in how intervention messages disseminate through social networks and which strategies are used to stimulate or discourage health behaviors in social networks. The *Social Buzz* data can be exported (from January 2018) into four separate data log files in which 1) group and individual messages are listed, 2) all given likes are listed which can be traced back to the source, 3) media exposure are listed (e.g., which video and duration of watching), and 4) a summary file is listed composed of several variables from the other 3 files. These log files are available on request.

#### Strategy of analysis

A variety of statistical techniques are used to address the project aims. In order to identify the most powerful influence agents traditional centrality measures (e.g., indegree centrality) are utilized, as well as more advanced techniques capable of identifying influence agents, such as “greedy” search algorithms available in the KeyPlayer package in R (R Core Team, 2015) [44]. To examine similarity and social influence of health behaviors in youth’s social networks, dyadic modeling techniques, such as actor-partner interdependence models [45] and stochastic actor-oriented models of network and behavioral co-evolution are used [46]. These modeling techniques are specifically designed to account for the known interdependencies in relational data. The stochastic actor-oriented models are particularly useful because of their capability to initially assess similarity in health behavior among friends, and also to disentangle processes associated with peer selection (i.e., creating or dissolving relationships on the basis of health behaviors) from peer influence (i.e., youth adapting the health behaviors of their peers).

In order to investigate which factors determine youths’ network positions as well as their energy intake and expenditure, multiple linear regression analyses, multilevel regression analyses, structural equation models (SEM) and mixed effect models are used to fit the observed data to theoretical constructs, and test the predicted relationships. Due to the innovative features of this project, some of the generated data require exploratory data analysis and sometimes without golden standards to refer to (e.g., *Social Network Beacon* data). Analyses are conducted with various statistical programs, including SPSS (version 24; IBM Corp., 2016), Mplus (7) [47], and R (R Core Team, 2015).

## Discussion

The *MyMovez* project-Phase I is a comprehensive multidisciplinary research project that extends existing knowledge by investigating the interplay between social network influences in relation to individual and environmental factors for youth’s energy-balance behaviors in a contemporary social media landscape. Moreover, the cross-sequential design allows for the assessment of changes within participants over time as well as differences between the two age cohorts. This pioneering project explores new standards for social network research, processing data and eventually the implementation of media health campaigns (Phase II of the project). The systematic way in which youth’s social networks are investigated by focusing on different social network aspects (i.e., types of questions and centrality measures for each of the health behaviors) in conjunction with individual and environmental (physical, social, and media) factors make this research project unique. The *MyMovez* project contributes to theory development by bringing together several approaches and theories of media and marketing effects, behavioral change, socialization, and network dynamics [8, 26, 32, 34]. In addition, this project develops the *Wearable Lab* by which the findings do not rely solely on self-reported measures but also on objective and real-time measures. The Wearable Lab supports keeping youth motivated and engaged to participate in the *MyMovez* project by adding a modern and fun factor.

There are some limitations to be discussed concerning Phase I of this project. For example, participation in the *MyMovez* project requires obtaining active consent from school principals, parents/legal guardians, and participants. Although the enrollment procedure is made as easy as possible (e.g., through online registration via a link or QR code as well as paper-and-pencil forms), we experience that parents/legal guardians are occupied with their daily routines and often forget to enroll their child. In addition, some parents/legal guardians may find the project too engaging or even intrusive. As a result, participation rates differ within classes. Participation rates lower than 60% per class affect social network analysis, leading to less power and validity of the results [48]. In addition, it is quite common that in longitudinal research, participation rates vary across data waves due to attrition and in our case because participants can enter each wave or do not finish the 7-day research period. Missing data can cause restrictions on the validity of the research findings; however, having obtained some participant data enables imputing missing data to solve this limitation. Another challenge in this exploratory project is the innovativeness of the methods used. For example, the *Social Beacon Network*, activity tracking among young people, using real-time data and social chats and photos require unconventional data analysis strategies and management protocols. The *MyMovez* project team takes great care of keeping up to date with current developments and is open for collaborations with other researchers.

In sum, the *MyMovez* project contains a rich data set that allows to investigate how various social influences co-determine youth’s energy intake and expenditure in combination with individual, psychosocial and environmental factors. The technological features of the *Wearable Lab* advances research due to the development of novel analytical and research strategies and the added fun-factor that contributes to the motivation of the participants. The project is theoretically and methodologically pioneering and will produce a unique and feasible method for improving large-scale media health campaigns. The *MyMovez* project-Phase I will give new theoretical and practical directions to scientific settings and intervention studies using social network interventions.

